### Ethical considerations

A key ethical consideration is the extensive time requirement of participants over a period of three weeks. Given this, we will recruit primarily university students in the first study, since they are likely to have time. For patients with affective disorders, the extensive time requirement may be overwhelming. Therefore, we decided to give patients up to two days off (Saturday and Sunday) every week, (in contrast with only one day off for healthy participants, leading to a total of 16—as opposed to 18 in sub-study 1—treatment sessions over three weeks. We are monitoring patients’ mood state at continuous basis with daily brief monitoring of subjective state and any adverse reactions through the VAS and ESQ questionnaires and weekly mood ratings assessed with HDRS and YMRS, respectively. If patients show mood symptom exacerbation to a score of ≥ 18 on the HDRS or YMRS, they are followed up with one more rating after two days, and if no improvement is seen, they are referred to their psychiatrist and drop-out is considered. In our experience, patients with affective disorders generally find it meaningful to take part in cognition trials because of their intrinsic motivation to try new treatments that may reduce their debilitating cognitive difficulties. This has so far ensured high adherence to and satisfaction with study participation.

To minimize attrition and ensure motivation, we have chosen an online cognitive training program and matched computer games that are highly engaging, rewarding, and—for the active condition—neuroadaptive (for more details, see [52]). Finally, fMRI is non-invasive, and PET [^11^C]UCBJ will be associated with small exposure to radioactivity, not much more than the annual background radiation. PET [^11^C]UCBJ has been found safe in studies examining synaptic density in healthy adults [84], in adolescents [71] and in patients with Alzheimer’s disease [85] or depression [86].

To ensure participant safety, all personnel on the project are certified in assessing and addressing suicidal thoughts and behavior through their completion of a suicide prevention course provided by the Capital Region of Denmark (must be renewed at a regular basis). If suicidal thoughts or behavior are detected during a mood rating, the clinician will perform a thorough screening for suicidal risk and contact the participant’s doctor. In acute situations, the clinician will escort the suicidal patient to a psychiatric emergency room via taxi. It is thereby ensured that any participant with mood symptoms, including suicidal thoughts and behavior during their participation in the study is cared for responsibly. Every participant is further under the coverage of the public insurance institution, the Patient Compensation Association.

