Sub-study 2 involves two intervention groups: (1) normobaric hypoxia (12%) combined with cognitive training 3.5 h daily, five to six days per week for three weeks (16 sessions in total), and (2) treatment as usual (TAU) in an assessor-blind controlled design. Patients in the TAU group will initially be assessed at the same time points as the active group with neurocognitive testing at baseline, week 4, and week 8, fMRI at baseline and week 8, and PET in week 4. After completed testing at week 8, patients in the TAU group undergo the three-week active intervention, followed by one additional neurocognitive assessment and mood rating in the week after treatment completion. The inclusion of this TAU arm rather than an active control group was chosen to ensure patient motivation and minimize attrition in this time-intensive study. Similar study designs with TAU control groups are common in pro-cognitive intervention studies investigating novel treatments in mood disorders and schizophrenia [39, 40]. Although patients will not be blinded to their allocated treatment arm, neurocognitive test results are generally not susceptible to placebo effects [41, 42] and assessments will be carried out by blinded, fully trained research assistants (psychology students).

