**Intervention and safety outcomes**						
Repeated moderate hypoxia exposure or normoxia (3.5 h per day, five to six days per week for three weeks)			x			
Cognitive training or sham training (3.5 h per day, five to six days per week for three weeks)			x			
Blood sampling (blood counts)	x	x	x (days 1, 8, and 19)	x	x	
Safety monitoring and assessments of potential adverse events		x	x	x	x	/
Mood ratings (HDRS + YMRS)	x	x		x	x	/
ESQ			x			
VAS			x			

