### Safety procedures and monitoring of hypoxia training

The procedure involves repeated exposure to normobaric 12% O_2_, which corresponds to an altitude of 4400 m. Similar daily repeated exposures to simulated altitudes of 4–8000 m over days to weeks are used widely, including by the US army, to induce high-altitude acclimatization and minimize risk of altitude sickness upon subsequent ascend to high altitudes [82]. We therefore evaluate the risk of altitude sickness in our study as minimal. Nevertheless, as safety precautions, we will (i) apply a 30-min lead-in phase, where oxygen levels are reduced slowly from 16 to 12% to allow for physiological adjustment; (ii) exclude individuals with risk factors for altitude sickness; (iii) monitor potential symptoms of altitude sickness at a daily basis with the Environmental Symptoms Questionnaire (ESQ) related to cerebral function [83]; and (iv) collaborate with medical doctors at the Frederiksberg Hospital ([name], [name], [name]) as in our previous EPO intervention studies. We will report the mean ESQ scores in the primary outcome articles in addition to any adverse events that may occur during the intervention.

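### In sub-study 2 the ESQ has no pre-exposure or concurrent TAU value, and adverse events are elicited more often in the hypoxia arm, so raw counts by arm would differ through ascertainment alone

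*Protocol article*

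**What the plan says.** All references are to the Protocol article.

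- **Sessions.** Study design and procedure gives the sub-study 2 hypoxia arm training "five to six days per week for three weeks (16 sessions in total"). TAU patients receive the same intervention only after their week 8 testing.
- **TAU contacts.** The same section states: "Patients in the TAU group will initially be assessed at the same time points as the active group with neurocognitive testing at baseline". The later testing points it names are weeks 4 and 8; fMRI is planned for baseline and week 8, PET for week 4. It describes no other TAU contact before crossover.
- **Symptom instruments.** Safety procedures and monitoring of hypoxia training lists, as a precaution, to "monitor potential symptoms of altitude sickness at a daily basis with the Environmental Symptoms Questionnaire (ESQ) related to cerebral function". Ethical considerations adds "daily brief monitoring of subjective state and any adverse reactions through the VAS and ESQ questionnaires". The same paragraph also mentions "weekly mood ratings assessed with HDRS and YMRS, respectively". Both are written for patients in general, with no arm named.
- **Table 1.** ESQ and VAS are marked only in the active treatment phase, not at baseline, week 4 or week 8. The row "Safety monitoring and assessments of potential adverse events" is marked at baseline, in the treatment phase, at week 4 and at week 8 (and at week 12 for sub-study 2), without a split by arm. HDRS and YMRS are not marked in the treatment phase.
- **Reporting.** "We will report the mean ESQ scores in the primary outcome articles in addition to any adverse events that may occur during the intervention".

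**The concern.** In patients, the instruments that bring symptoms and adverse reactions to light are tied to attending a session, and during the randomised comparison only one arm attends sessions. Two things follow.

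First, the mean ESQ in the patient article would stand alone. With no scheduled value before exposure and none from TAU patients over the same weeks, symptoms of hypoxia cannot be separated from symptoms the patients would have had anyway. Background symptoms are plausible: patients may enter with HDRS-17 and YMRS scores up to 14, and the Limitations section says most are on psychotropic medication.

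Second, adverse events reported in a two-arm randomised article will be read by arm. More frequent questioning in one arm yields more reports there even if the true rates are equal.

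What is at stake is the safety reading of a novel intervention in patients, for which the Limitations section treats participant safety as the principal concern. TAU symptoms that were never asked about cannot be recovered at the analysis stage.

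**Working it through.** **1. Session count.** Five to six days a week for three weeks gives 5 × 3 = 15 to 6 × 3 = 18 sessions. The stated 16 lies in that range, for example 5 + 5 + 6 = 16. Daily monitoring at sessions therefore means 16 scheduled occasions per hypoxia patient.

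**2. Scheduled elicitation before TAU crossover, by arm.**

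| Item | Hypoxia + training | TAU |
|---|---|---|
| ESQ/VAS at baseline | not marked | not marked |
| ESQ/VAS in weeks 1 to 3 | daily, 16 sessions | none described |
| ESQ/VAS at weeks 4 and 8 | not marked | not marked |
| Adverse-event assessment at baseline, weeks 4 and 8 | marked | marked |
| Weekly HDRS/YMRS in weeks 1 to 3 | in Ethical considerations, not in Table 1 | arm not stated; not in Table 1 |

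The ESQ is thus scheduled at no time point common to both arms. Adverse-event assessment is common at three visits.

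**3. Effect on event counts.** The documents give no symptom rate, so the following is an assumption. Each time a patient is questioned, a report arises with probability p, the same in both arms (no true difference) and independent between occasions. The chance of at least one report in k occasions is 1 − (1 − p)^k, and with 30 patients per arm the expected number is 30 times that. By week 4:

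- hypoxia arm: k = 16 sessions + week 4 = 17
- TAU, if the weekly mood ratings also cover TAU and count as questioning: k = 3 + 1 = 4
- TAU, week 4 only: k = 1

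Worked line for p = 0.05: 1 − 0.95^17 = 0.582, giving 17.5 of 30; 1 − 0.95^4 = 0.185, giving 5.6 of 30; 0.05 gives 1.5 of 30.

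| p (assumed) | Hypoxia, k = 17 | TAU, k = 4 | TAU, k = 1 |
|---|---|---|---|
| 0.01 | 4.7 | 1.2 | 0.3 |
| 0.02 | 8.7 | 2.3 | 0.6 |
| 0.05 | 17.5 | 5.6 | 1.5 |
| 0.10 | 25.0 | 10.3 | 3.0 |

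Even on the reading kinder to the plan (k = 4), the arms differ with no true effect. The direction does not depend on p; the size does. Positive correlation between a patient's days would shrink the gap, and so would a week-4 question that looks back over several weeks and picks up more than a same-day question does.

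**4. What this arithmetic does not cover.** It concerns the number of patients with at least one event. A mean ESQ score does not rise merely because the form is given more often. For the ESQ the problem is the missing reference value shown in step 2.

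**The case against.** The strongest case for the plan has five parts.

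- **TAU contact.** A reader might infer that TAU patients have no contact at all between baseline and week 4, so that questioning is 16 occasions against zero. The article does not say so. The listed TAU time points cover cognitive testing and imaging, the weekly mood ratings name no arm, and Table 1 does not split adverse-event monitoring by arm. This stands. What can be said is that no ESQ or session-based elicitation is described for TAU before crossover. Mood ratings are in any case neither the ESQ nor an adverse-event questionnaire.
- **No planned comparison.** A reader might also infer that the article will compare harms formally, or show almost no events in TAU. No between-arm harm test is stated, the promised reporting is descriptive, and adverse events are assessed in both arms at week 4. This stands too. It removes any charge of a biased test, but not the likelihood that events will be read by arm.
- **Purpose of the ESQ.** It is there to detect altitude sickness, so giving it during exposure fits. That is true, but a tolerability score without a pre-exposure value remains hard to interpret.
- **Sub-study 1 as control.** Its two normoxia arms attend the same kind of session under double-blinding, and Table 1 marks the ESQ in both sub-studies. This gives a fair estimate of hypoxia-related ESQ excess in healthy people. It cannot give the background rate in patients with affective disorders.
- **Detail left to the full protocol.** How adverse events are asked about, and whether the day 1 form precedes room entry, may be settled there. The time points at which the ESQ is given are, however, set out in Table 1.

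**Conclusion.** The point holds in a limited form. Followed as written, the sub-study 2 article will report a mean ESQ with no scheduled pre-exposure value and no concurrent TAU value, and raw adverse-event counts by arm that differ through unequal ascertainment. Under the assumed per-occasion probabilities of 0.01 to 0.10 with no true difference, the expected numbers of patients with at least one report by week 4 run from 4.7 against 1.2 up to 25.0 against 10.3 of 30 if TAU has weekly contact. The gap is wider if TAU is asked only at week 4. These figures rest on equal and independent report probabilities that are not in the documents; they show direction and plausible scale, not a prediction.

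The cognitive outcomes are not affected. The common adverse-event assessments at baseline, week 4 and week 8 remain usable. A separate inconsistency needs settling: Ethical considerations describes weekly HDRS and YMRS ratings, while Table 1 marks none in the treatment phase. This should be changed because the change is cheap, not because it threatens the primary result.

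**What to change.** 1. In sub-study 2, give the ESQ to both arms at baseline (before any exposure), week 4 and week 8, alongside the adverse-event assessment already scheduled there.
2. Send TAU patients a short ESQ and adverse-event form through REDCap in weeks 1 to 3.
3. Base any between-arm statement on harms only on data collected on the schedule common to both arms.
4. Report the daily session ESQ and session events as single-arm data, with the ESQ as change from the pre-exposure value.
5. For patients already treated without these forms, state in the article that ascertainment differed by arm.
6. Reconcile the weekly HDRS/YMRS ratings in Ethical considerations with Table 1, and state which arm they cover.

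The cost is a few minutes of patient time at existing visits and a few remote prompts for TAU patients; questionnaires already go directly into REDCap. Patients already enrolled will lack the added forms: 33 of the planned 60 were included by April 2024, leaving 60 − 33 = 27 at that date, with recruitment due to end in June 2025. If enrolment has finished, items 3, 5 and 6 can still be done in full, and the single-arm labelling in item 4 still applies.

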### Perspectives

This is a project that has the potential to unravel a novel mechanism of enduring neuroplasticity and long-term improvement in cognitive functions, which can contribute to the current understanding of brain plasticity and unlock novel effective treatments for cognitive decline. With the multidisciplinary approach, the project can lead to a mechanistically informed therapeutic approach targeting cognitive impairments across patients with neuropsychiatric disorders.

Version and date identifier: Protocol article version 1, 22 April 2024.

## Data Availability

The datasets used and analyzed in the current study are available from the corresponding author upon reasonable request.

## Abbreviations

ABCR: Action-Based Cognitive Remediation
AQoL: The Assessment of Quality of Life
BD: Bipolar disorder
BMI: Body mass index
CANTAB: Cambridge Neuropsychological Test Automated Battery
CAVIR: Cognition Assessment in Virtual Reality
COBRA: Cognitive Complaints in Bipolar Disorder Rating Scale
DART: Danish Adult Reading Test
DMN: Default mode network
dPFC: Dorsal prefrontal cortex
ECT: Electroconvulsive therapy
EPO: Erythropoietin
ERT: Emotion recognition test
ESQ: Environmental Symptoms Questionnaire
FAST: Functional Assessment Short Test
FEAT: FMRIB Expert Analysis Tool
fMRI: Functional magnetic resonance imaging
FSL: FMRIB Software Library
HIF: Hypoxia inducible factor
HDRS-17: Hamilton Depression Rating Scale – 17 items
ISBD: International Society for Bipolar Disorder
ITT: Intention-to-treat
MRI: Magnetic resonance imaging
NEAD: Neurocognition and Emotion in Affective Disorders Centre
O_2_: Oxygen
OTS: One Touch Stockings of Cambridge
PET: Positron emission tomography
RAVLT: Rey Auditory Verbal Learning Test
RBANS: Repeatable Battery for the Assessment of Neuropsychological Status
RVP: Rapid Visual Information Processing
SCAN: Schedules for Clinical Assessment in Neuropsychiatry
SCIP-D: Screen for Cognitive Impairment in Psychiatry – Danish version
SD: Standard deviation
SDS: Sheehan Disability Scale
SV2A: Synaptic vesicle glycoprotein 2A
SWM: Spatial working memory
TAU: Treatment as usual
TMT-A: Trail Making Test A
TMT-B: Trail Making Test B
UD: Unipolar disorder
VR: Virtual reality
WAIS-III LNS: Wechsler Adult Intelligence Scale Version III Letter–Number Sequencing
WCST: Wisconsin Card Sorting Task
WHOQOL-BREF: World Health Organization’s Quality of Life Assessment
WSAS: Work and Social Adjustment Scale
YMRS: Young Mania Rating Scale
